### Adverse events and safety reporting

**
*Tolerability and safety*
**

Metformin is an inexpensive first-line anti-hyperglycaemic drug for type 2 diabetes mellitus (T2DM). Worldwide, it is the most widely prescribed drug to treat T2DM, and has an excellent safety record. Over the past decades, it has been given to more than 120 million people. Metformin effectively lowers the blood glucose levels by increasing insulin sensitivity and by inhibiting hepatic gluconeogenesis and is not associated with hypoglycaemia in T2DM-patients nor healthy subjects. Previous studies of metformin as adjunct HDT in non-diabetics have used dosages ranging from 1000–2000mg/day
^
27,
43,
66–
68
^. Metformin offers a favourable tolerability and a high level of patient acceptance. It is commonly used in combination with other drugs because of its beneficial profile. It does not inhibit or induce any CYP-enzyme and is eliminated unchanged in the urine. The trial sponsor has an insurance policy in place in the event of any participant suffering harm as a result of their involvement in the research.

**
*Adverse events*
**

The main side-effects of metformin are gastro-intestinal and the risk of lactic acidosis. Approximately 10% of patients report gastrointestinal side-effects, including diarrhoea, cramps, nausea and increased flatulence. Symptoms are typically mild and transient, peaking at the initiation of metformin, and often resolve spontaneously despite continued treatment and dose escalation. Symptoms subside when administered with meals. The reported incidence of metformin-associated lactic acidosis is very low (approximately 0.03 cases/1000 patient-years, with approximately 0.015 fatal cases/1000 patient-years)
^
61,
62,
69
^. In more than 20,000 patient-years exposure to metformin in clinical trials there were no reports of lactic acidosis. Reported cases occurred primarily in diabetic patients with significant renal insufficiency, often in the setting of multiple concomitant medical/surgical problems and multiple concomitant medications. A Cochrane review of 347 comparative trials and cohort studies with a combined 70,490 patient-years of metformin exposure identified no cases of fatal or non-fatal lactic acidosis
^
46
^. Metformin does not cause hypoglycaemia in normoglycemic individuals. Rifampicin may enhance the glucose-lowering effect of metformin in non-diabetic individuals by increased hepatic expression of OCT1, resulting in increased metformin delivery to the liver
^
70
^. Importantly, the combination of rifampicin plus metformin did not reduce baseline blood glucose values or cause hypoglycaemia and rifampicin exerts a countervailing effect by boosting intestinal glucose absorption. A study in TB-patients with DM reported that rifampicin increased metformin plasma levels with 17–30%, but did not alter blood glucose levels
^
71
^. The interaction between rifampicin and metformin, however, will be of less significance in our population, as rifampicin is only given once a month at a dose of 600 mg, whereas in TB it is given daily. No interactions are known between metformin and dapsone or clofazimine. We will minimize the risk of AEs in the trial by excluding candidates with a history of renal or liver insufficiency and DM, by counselling at enrolment and follow-up visits regarding the need to maintain adequate caloric intake, and counselling regarding the symptoms of hypoglycaemia and the actions to take if these symptoms occur.

**
*Dose modifications*
**

Possible IMP-related AEs will be managed in both randomized groups according to standard clinical practice. Additional requirement of the dose modification will be determined on a case-by-case basis by the attending physician according to the clinical circumstances and guidelines. If treatment is discontinued due to an AE, the investigator will arrange for follow-up visits until the AE has resolved or stabilised. Wherever possible, dose modifications should be performed without unblinding. Participants will not be put at any additional risk by trial randomization, as any participant who develops a suspected adverse drug reaction to the IMP will be managed as if they were receiving metformin.

**
*Safety reporting*
**

The principles of ICH GCP apply to this study protocol. All grade 3 or 4, or serious AEs and adverse reactions (ARs), whether expected or not, will be recorded. Non-serious grade 1 or 2 AEs will only be recorded in case they are thought to be related to the IMP or if they result in a change or interruption in MDT. When an AE or AR occurs, the study team and site PI responsible for the care of the participant first assess whether or not the event is serious. If the event is serious and not only related to leprosy, or is fatal, then a SAE form must be completed and the coordinating centre (OUCRU ID) notified within 24 hours. The severity of all AEs and/or ARs (serious and non-serious) in this trial should be graded using the toxicity gradings following Common Toxicity Criteria for Adverse Events CTCAE version 5.0
^
72
^.

All AEs will be assessed for seriousness, causality and expectedness. Causality in relation to the IMP includes five categories: unrelated, unlikely, possible, probable, and definitely related. If the causality assessment is unrelated or unlikely to be related, the event is classified as an SAE. If the causality is assessed as possible, probable or definitely related, then the event is classified as an SAR. Expectedness of the AE is assessed using the summary of medicinal product characteristics (SMPC). An unexpected adverse reaction is one not previously reported in the current SMPC at the time the event occurred, or one that is more frequent or more severe than previously reported. If a SAR is assessed as being unexpected, it becomes a suspected unexpected serous adverse reaction (SUSAR).

All applicable SAE/SAR will be reported to the ethics committee and the Indonesian regulatory authority by OUCRU ID based on the requirements stipulated in the Head of BPOM RI Regulation No. 21 year 2015 on Clinical Trial Conduct (Peraturan Kepala Badan Pengawas Obat dan Makanan Republik Indonesia (BPOM RI) tentang Tata Laksana Uji Klinik); and/or relevant local regulations. Any applicable subsequent update to the regulation will be adhered to, respectively.

The trial will be monitored by an independent Data Monitoring Committee (DMC) who will oversee the safety and progress of the trial and provide recommendations to the Trial Management Group (TMG) and sponsor. The DMC will meet periodically according to the DMC charter and will review the safety and efficacy of IMP after 50% of targeted recruited numbers have been included in the trial. The DMC will have full access to the unblinded data.

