### Outcomes

**
*Primary efficacy outcome*
**

The proportion of participants experiencing a LR during study follow-up (total 48 weeks).

**
*Primary safety outcome*
**

The proportion of participants with at least one adverse event (AE) within the first 24 weeks of the study.

**
*Secondary outcomes*
**

1.   The proportion of participants experiencing a T1R or T2R (as separate outcomes) at 24 and 48 weeks.

2.   Time to first LR and time to first T1R and T2R as separate outcomes, over the full 48 weeks.

3.   Severity of T1R and T2R at onset based on investigator-assessed validated Clinical Severity Scores
^
52,
53
^.

4.   The proportion of participants with at least one SAE within the first 24 weeks of the trial.

5.   The total number of AE within the first 24 weeks of the trial.

6.   Cumulative corticosteroid usage in participants with a leprosy reaction.

7.   The proportion of participants experiencing clinical nerve function impairment (NFI) developed over the full 48 weeks.

8.   Quality of Life (QoL) at enrolment, half-way treatment intervention (12 weeks), end of treatment intervention (24 weeks), and end of study (48 weeks) using validated local language versions of the Dermatology Life Quality Index (DLQI) and the 36-item Short Form Survey (SF-36).

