**Research Samples**																	
Skin biopsy (6 mm)		X														X	1
Serum (4 mL)		X	X	X		X			X			X			X	X	7
EDTA blood (4 mL)		X		X		X			X							X	4
PAXgene® tube (2.5 mL)		X	X													X	2
Total blood volume for research (mL)		10.5	6.5	8		8			8			4			4	10.5	49

In addition to the scheduled study visits at fixed timepoints (outlined above), additional unscheduled visits may take place in case of a LR, adverse events or any other medical complaints and will be recorded as such. Abbreviations: ALT, alanine transaminase; ID, identification; IMP, investigational medicinal product; LR, leprosy reaction; MDT, multi-drug therapy. a. Physical examination includes body weight, height, blood pressure and nerve function assessment, incl. nerve palpation, sensory testing with five Semmes-Weinstein monofilaments at designated test sites on hands and feet and voluntary muscle power graded using the modified Medical Research Council scale. b. Assessment of treatment adherence to IMP (until week 24) and MDT (to week 48). c. Suspect for diabetes: if random blood glucose is elevated ≥200 mg/dL (or ≥11,1 mmol/L) or fasting blood glucose ≥ 126 mg/dL (or ≥7.0 mmol/L). d. HIV-screening only applicable for participants in Papua.

**
*Clinical assessments*
**

During each study visit the following procedures will be undertaken (
Table 2):

■ Systematic evaluation of clinical symptoms and physical examination including nerve function assessment established through nerve palpation, sensory testing and voluntary muscle testing.■ Assessment of adherence to IMP (until week 24, W24) and MDT (until W48) through (i) a brief adherence questionnaire; (ii) pill counts on pharmacy records; and (iii) collection of treatment diaries and distribution of new diaries to each patient by the pharmacist; and (iv) clinical criteria hyperpigmentation and ichthyosis (extensor surfaces).■ Record all AEs and SAEs during the first 24 weeks when IMP is given. The severity and likely relationship of these AEs to metformin will be assessed and documented by the study team, chief investigators and/or study coordinator.■ Assessment of LR and its severity using standard case definitions and validated severity scales
^
52,
53
^.■ Assessment of QoL-questionnaires (at pre-specified study visits).

**
*Laboratory assessments*
**

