The primary efficacy outcome is the proportion of participants experiencing a LR during study follow up (total 48 weeks). The effect measure is the treatment difference between the intervention (metformin plus MDT) and control (placebo plus MDT) group. The treatment difference will be quantified in a logistic regression model that includes BI as a continuous variable and study site. Results will be marginalized over BI and study site. We will also consider a model using a log-link, which provides risk ratios. If loss to follow-up is 5% or more, we will take censored data into account and fit the model using pseudo-values. The heterogeneity of the treatment effect will be assessed by including an interaction term between treatment and BI, as well as between treatment and study site (two separate models). For the safety outcome, the proportion of participants with at least one AE within the first 24 weeks will be compared. The chi-squared test will be used to compare the treatment arms, or Fisher’s exact test in case the expected number under the null hypothesis in at least one of the cells is smaller than one. The analyses to be performed will be documented in the Statistical Analysis Plan (SAP), which will be finalized before the database is unlocked and the final analysis with the unblinded data is performed. R software will be used.

**
*Analysis of the secondary outcomes*
**

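### The protocol gives two incompatible adverse-event recording rules for weeks 0-24 and does not settle which one feeds the primary safety outcome

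*Protocol article*

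**What the plan says.** Outcomes defines the primary safety outcome as "The proportion of participants with at least one adverse event (AE) within the first 24 weeks of the study". Secondary outcome 5 is the total number of AEs over the same period. Neither is limited by grade or relatedness. The Statistical analysis section keeps that form: "the proportion of participants with at least one AE within the first 24 weeks will be compared".

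Two places say what is recorded:

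- Data collection, Clinical assessments (procedures at each visit): "Record all AEs and SAEs during the first 24 weeks when IMP is given".
- Adverse events and safety reporting, Safety reporting: "All grade 3 or 4, or serious AEs and adverse reactions (ARs), whether expected or not, will be recorded". It then adds: "Non-serious grade 1 or 2 AEs will only be recorded in case they are thought to be related to the IMP", with the alternative condition "or if they result in a change or interruption in MDT".

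On serious events, Safety reporting also says: "If the causality assessment is unrelated or unlikely to be related, the event is classified as an SAE". Events judged possibly, probably or definitely related are labelled SAR, and unexpected ones SUSAR. Secondary outcome 4 is "The proportion of participants with at least one SAE within the first 24 weeks of the trial".

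**The concern.** An any-AE proportion and an AE count both need every AE to be on record. One section promises that; the other removes a class of mild events by attribution. The class matters because the protocol expects metformin's side-effects to be mainly gastrointestinal, reported by about 10% of patients and typically mild, so they sit in the grades where the rules diverge. Under the narrower rule, whether such an event counts towards a primary outcome turns on whether someone thinks the IMP caused it. A final report of participants with at least one AE would then describe a different quantity from the one measured.

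An analysis plan cannot repair this later, because events that were never recorded cannot be recovered. Trial status says enrolment is under way at both groups of sites.

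**Working it through.** No stated figure is at issue, so the check is a comparison of the two rules by type of event in weeks 0-24.

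| Event | Clinical assessments | Safety reporting |
|---|---|---|
| Serious, any grade or cause | recorded | recorded |
| Non-serious, grade 3 or 4 | recorded | recorded |
| Non-serious, grade 1-2, thought IMP-related | recorded | recorded |
| Non-serious, grade 1-2, thought unrelated, MDT changed or interrupted | recorded | recorded |
| Non-serious, grade 1-2, thought unrelated, MDT unchanged | recorded | not recorded |

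The rules differ only in the last row, and there they contradict each other. A participant whose only events fall in that row has the primary safety outcome under one rule and not under the other. Each such event also adds one to outcome 5 under one rule and nothing under the other.

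Under the narrower rule the measured quantity is therefore at least one AE that is grade 3 or higher, serious, judged IMP-related or MDT-altering. The boundary between the third and fifth rows is the causality judgement.

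**Scale, on assumed rates only.** The documents give no AE rate for this population. Let b be the risk of an unrelated AE in both arms and r the risk of a related AE, taken as independent, so the any-AE risk is 1 - (1 - b)(1 - r). Assume that a tenth of b is still recorded under the narrower rule. With b = 40% and r = 20% on metformin against 5% on placebo:

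- All AEs recorded: 1 - 0.60 × 0.80 = 52.0% against 1 - 0.60 × 0.95 = 43.0%, a difference of 9.0 points.
- Narrower rule, b = 4%: 1 - 0.96 × 0.80 = 23.2% against 1 - 0.96 × 0.95 = 8.8%, a difference of 14.4 points.

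For b from 20% to 60%, and r of 10% against 2%, 20% against 5% or 30% against 10%, the metformin-arm risk is 28-72% with all AEs and 12-34% under the narrower rule. The differences are 3-16 and 8-20 points.

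This assumes that every related event is attributed and recorded. If only a share q is, the difference in the worked case becomes 0.96 × 0.15 × q = 0.144q. That falls below 9.0 points once q is under 0.090/0.144 = 62.5%. The level of the outcome depends on the rule throughout these assumptions; the direction of the change in contrast does not stay fixed.

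**The case against.** - **A hierarchy can be read in.** The record-all instruction is one bullet in a list of visit procedures, while Safety reporting is the dedicated section with the detailed rule. Sites work from protocol version 5.0, which is not shown. This stands to the extent that a reader may not infer that sites are actually following different rules: the documents say nothing about conduct. But if Safety reporting governs, the outcome definitions are the text that is wrong, so the inconsistency only moves.

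- **The stated outcome may well be captured.** This is correct. A reader might conclude that the any-AE outcome is not being measured; that follows only under the narrower rule.

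- **Attribution need not bias the arms.** The trial is double-blind and randomisation is stratified by site, so differing attribution habits should fall on both arms. For serious events a possible relation already counts as related, and suspected reactions are managed as if the participant were on metformin, so mild gastrointestinal events are likely to be attributed and recorded. This stands against any claim of differential bias. It does not restore the stated outcome.

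- **Lost power or a hidden signal.** A reader might infer that the narrower rule conceals harm. With full attribution the assumed rates give the larger contrast under that rule, so the documents do not support this. What changes is the quantity being estimated.

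- **Outcome 4.** Read literally, the SAE and SAR labels suggest that outcome 4 omits drug-related serious events. That reading is not supported. Safety reporting requires an SAE form for any event that is fatal, or serious and not only leprosy-related, before causality labels are applied, and it records all serious AEs and ARs. No drug-related serious event is lost; only the label is loose.

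**Conclusion.** The inconsistency is real and explicit. Clinical assessments and Safety reporting cannot both apply to a non-serious grade 1-2 event thought unrelated that leaves MDT unchanged, and the article does not say which prevails. The primary safety outcome and outcome 5 depend on the answer. If the Safety reporting rule is in use, both outcomes are misdescribed, and for mild events they rest on an attribution judgement.

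The reach is limited. Serious and grade 3-4 events are unaffected, as is the primary efficacy outcome. The numerical size is unknown because it depends on AE rates that the documents do not give. The conclusion rests on the wording alone and not on the illustrative rates. The outcome 4 label is a minor wording point.

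**What to change.** First establish which rule sites have been using, since enrolment has started. Then reconcile the two sections in one of two ways:

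1. **Record all AEs in weeks 0-24.** Remove the attribution condition from Safety reporting for that period and leave the outcomes as they are. Cost: more CRF entries. If the narrower rule has been in use so far, events already left unrecorded would make the early data differ from the later data, and that would have to be stated.
2. **Keep the Safety reporting rule.** Correct the Clinical assessments bullet. Restate the primary safety outcome as participants with at least one AE that is grade 3 or higher, serious, judged IMP-related or MDT-altering, restate outcome 5 as the number of such AEs, and carry the wording into the Statistical analysis section. Cost: wording only, but a narrower safety claim.

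In either case, add one sentence to outcome 4 saying that it counts all serious events whatever their causality label (SAE, SAR or SUSAR). This costs nothing beyond the wording.

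### The protocol uses SAE in two senses, so secondary outcome 4 can be read as leaving out serious events attributed to the study drug

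*Protocol article*

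**What the plan says.** The protocol article (Adverse events and safety reporting, Safety reporting) classifies serious events by their judged relationship to the study drug. For the two lower causality categories: "If the causality assessment is unrelated or unlikely to be related, the event is classified as an SAE". For the three upper ones: "If the causality is assessed as possible, probable or definitely related, then the event is classified as an SAR". A SAR that is also unexpected becomes a SUSAR. As worded, the SAE and SAR labels are mutually exclusive.

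Secondary outcome 4 (Outcomes) is: "The proportion of participants with at least one SAE within the first 24 weeks of the trial". It mentions neither SARs nor SUSARs.

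Elsewhere the term is broader. Earlier in Safety reporting, site staff decide first whether an event is serious, and then: "If the event is serious and not only related to leprosy, or is fatal, then a SAE form must be completed". Relationship to the study drug plays no part in that step. On recording, the section says: "All grade 3 or 4, or serious AEs and adverse reactions (ARs), whether expected or not, will be recorded". Under Data collection, Clinical assessments, the instruction is "Record all AEs and SAEs during the first 24 weeks when IMP is given", followed by "The severity and likely relationship of these AEs to metformin will be assessed and documented".

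**The concern.** In the usual structure, an SAE is any serious adverse event, and a SAR is an SAE with a suspected causal link. The classification rule instead makes the two labels alternatives. A site that labels events by that rule, and an analyst who then counts the label named in outcome 4, would omit every serious event that the assessor linked to the study drug.

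Outcome 4 is the only listed outcome that compares serious harm between arms. The primary safety outcome and outcome 5 count AEs of any grade that qualify for recording, so a serious reaction is not distinguished there from a minor one. Events truly caused by metformin are the ones most likely to be judged at least possibly related. The narrow count would therefore remove events mainly from the metformin arm and pull the comparison towards no difference.

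**Working it through.** **1. The plan's own figure.** The protocol's only power figure concerns the efficacy outcome: 75 per arm, 50% versus 25%, two-sided 0.05, 89%. With the pooled-variance normal approximation, the null standard error is √(2 × 0.375 × 0.625 / 75) = 0.0791 and the alternative standard error is √((0.25 + 0.1875) / 75) = 0.0764. Then z = (0.25 − 1.96 × 0.0791) / 0.0764 = 1.24, which gives 89.3%. The figure reproduces. Nothing in this point depends on it, and the protocol gives no expected serious-event rate.

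**2. The two uses of SAE side by side.**

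| Place | What makes an event an SAE | Serious event judged related to study drug |
|---|---|---|
| Safety reporting, form rule | Seriousness (and not only leprosy, unless fatal) | Gets an SAE form |
| Safety reporting, classification rule | Causality unrelated or unlikely | SAR, not SAE |
| Data collection, Clinical assessments | All SAEs recorded, relationship assessed as an attribute | Remains a recorded event |
| Outcomes, secondary outcome 4 | Not defined there | Depends on which rule is used |

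The form rule and the classification rule give different counts for outcome 4 from the same data.

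**3. What the narrow count would do (assumed rates).** Let u be the background serious-event risk in both arms. Let r be the drug-caused risk on metformin only, independent of u. Take 166 / 2 = 83 per arm. Assume first that every drug-caused event is judged related and every background event is not.

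- Inclusive risk on metformin: m = 1 − (1 − u)(1 − r). Placebo: u.
- Narrow risk: u in both arms, so the expected difference is 0.
- Share of metformin participants with a serious event who are dropped: (m − u) / m.

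| u | r | m | Inclusive difference (points) | Narrow difference | Share dropped | Approximate power, inclusive |
|---|---|---|---|---|---|---|
| 2% | 2% | 4.0% | 2.0 | 0 | 49% | 11% |
| 2% | 5% | 6.9% | 4.9 | 0 | 71% | 33% |
| 2% | 10% | 11.8% | 9.8 | 0 | 83% | 71% |
| 5% | 2% | 6.9% | 1.9 | 0 | 28% | 7% |
| 5% | 5% | 9.8% | 4.8 | 0 | 49% | 21% |
| 5% | 10% | 14.5% | 9.5 | 0 | 66% | 54% |

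**4. Relaxing the attribution assumption.** If only half of the drug-caused events are judged related, about half of the difference survives. With u = r = 5%, the narrow difference is [1 − 0.95 × (1 − 0.025)] − 0.05 = 0.024, against 0.048 inclusive. If blinded assessors also call some background events possible, equally often in both arms, both narrow counts fall but the lost difference is not restored.

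**5. In counts.** Suppose 4 background cases per arm plus 4 drug-caused cases on metformin (assumed). The inclusive comparison is 8/83 (9.6%) versus 4/83 (4.8%), and the narrow one is 4/83 versus 4/83. Even the inclusive contrast is weak as a test: Fisher p = 0.37, uncorrected chi-squared p = 0.23. What is lost here is a descriptive signal, not a significant result.

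**The case against.** The strongest reply is that the narrow reading is not what the protocol intends. The SAE form is triggered by seriousness alone, so a serious event judged drug-related does generate one. Relationship to metformin is handled as an attribute of events already recorded. The Abstract refers to serious adverse events without a causality limit, and the Introduction applies the abbreviation SAE to harms caused by corticosteroids. The classification sentence sits in a reporting section that leads to SUSAR identification, and no sentence says that SARs are excluded from outcome 4. This stands: an inclusive reading is available and plausible. It does not remove the defect, because the only explicit classification of serious events says otherwise, and the section treats the two labels as parallel classes when it sets out what goes to the authorities.

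A reader might infer that the trial will lose serious drug reactions altogether. The documents do not support that. Serious AEs and ARs are all recorded with causality. Related events still fall under AE in the primary safety outcome ("The proportion of participants with at least one adverse event (AE) within the first 24 weeks of the study") and in outcome 5, and the DMC sees unblinded data.

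A reader might also infer a second, cumulative loss, because a non-fatal serious event due only to leprosy requires no SAE form. The two exclusions do not add up. Counting by form includes SARs, and counting by causality label includes leprosy-only events as unrelated. No sentence applies both filters at once. The form rule governs notification within 24 hours, and recording is covered separately.

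Finally, the SAP is not shown and may already settle the counting rule. That tempers the consequence, but the protocol's stated rule still needs correcting.

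**Conclusion.** The point holds as an inconsistency in a stated definition. One rule in Safety reporting ties SAE to seriousness; another reserves it for serious events judged unrelated or unlikely. Outcome 4 relies on the term without choosing between them. If the explicit classification is applied as written, serious events attributed to the study drug go uncounted and the comparison is biased towards no difference. The documents do not show that it will be applied that way.

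The size cannot be derived from the protocol. Under the assumed rates above, the narrow count would erase a true difference of 1.9 to 9.8 percentage points when all drug-caused events are recognised as related, and roughly half of it when half are. No sample size or power figure changes, and the inclusive count is recoverable from the recorded data.

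**What to change.** In Safety reporting, state that an SAE is any serious adverse event regardless of causality, that a SAR is an SAE judged possibly, probably or definitely related, and that a SUSAR is an unexpected SAR. In Outcomes, state that secondary outcome 4 counts all of these, and report the related subset alongside by arm. Settle the wording before unblinding and carry the same definition into the SAP.

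The cost is a sentence in each place. No new data are needed, since serious events and their causality are already recorded. The downside is a possibly slightly higher stated SAE count.
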